# Effects of a liquefied petroleum gas stove intervention on pollutant exposure and adult cardiopulmonary outcomes (CHAP): study protocol for a randomized controlled trial

**DOI:** 10.1186/s13063-017-2179-x

**Published:** 2017-11-03

**Keywords:** Cookstove, LPG, Indoor air pollution, Household air pollution, Personal exposure, Biomass fuel, Cardiopulmonary outcomes, Behavior change, Exclusive adoption

## Abstract

**Background:**

Biomass fuel smoke is a leading risk factor for the burden of disease worldwide. International campaigns are promoting the widespread adoption of liquefied petroleum gas (LPG) in resource-limited settings. However, it is unclear if the introduction and use of LPG stoves, in settings where biomass fuels are used daily, reduces pollution concentration exposure, improves health outcomes, or how cultural and social barriers influence the exclusive adoption of LPG stoves.

**Methods:**

We will conduct a randomized controlled, field intervention trial of LPG stoves and fuel distribution in rural Puno, Peru, in which we will enroll 180 female participants aged 25–64 years and follow them for 2 years. After enrollment, we will collect information on sociodemographic characteristics, household characteristics, and cooking practices. During the first year of the study, LPG stoves and fuel tanks will be delivered to the homes of 90 intervention participants. During the second year, participants in the intervention arm will keep their LPG stoves, but the gas supply will stop. Control participants will receive LPG stoves and vouchers to obtain free fuel from distributors at the beginning of the second year, but gas will not be delivered. Starting at baseline, we will collect longitudinal measurements of respiratory symptoms, pulmonary function, blood pressure, endothelial function, carotid artery intima-media thickness, 24-h dietary recalls, exhaled carbon monoxide, quality-of-life indicators, and stove-use behaviors. Environmental exposure assessments will occur six times over the 2-year follow-up period, consisting of 48-h personal exposure and kitchen concentration measurements of fine particulate matter and carbon monoxide, and 48-h kitchen concentrations of nitrogen dioxide for a subset of 100 participants.

**Discussion:**

Findings from this study will allow us to better understand behavioral patterns, environmental exposures, and cardiovascular and pulmonary outcomes resulting from the adoption of LPG stoves. If this trial indicates that LPG stoves are a feasible and effective way to reduce household air pollution and improve health, it will provide important information to support widespread adoption of LPG fuel as a strategy to reduce the global burden of disease.

**Trial registration:**

ClinicalTrials.gov, ID: NCT02994680, Cardiopulmonary Outcomes and Household Air Pollution (CHAP) Trial. Registered on 28 November 2016.

**Electronic supplementary material:**

The online version of this article (doi:10.1186/s13063-017-2179-x) contains supplementary material, which is available to authorized users.

## Background

Household air pollution (HAP), caused by the combustion of biomass fuels (typically wood, dung, and agricultural crop waste), is a leading contributor to the global burden of disease and the largest environmental risk factor for preventable disease [1–3]. HAP from biomass fuel smoke was estimated to be responsible for 4.3 million deaths in 2012 [4]. It has been associated with chronic bronchitis, chronic obstructive pulmonary disease (COPD) [5–13], lung cancer [14, 15], childhood pneumonia [16], acute lower respiratory infections [17, 18], cardiovascular events [19, 20], and low birthweight [21, 22]. Globally, nearly three billion individuals, 40% of all households and 90% of rural households use biomass fuels as their primary source of domestic energy [2]. Burning of biomass fuels for cooking is most pervasive in low- and middle-income countries (LMIC). Women and children have the highest risks of exposure to biomass fuel smoke, accounting for 60% of premature deaths from HAP in 2012 [23]. HAP may also have important effects on both cardiovascular and pulmonary health.

Cardiovascular disease (CVD) is the leading cause of morbidity and mortality worldwide [24]. More than 80% of CVD deaths occur in LMICs, where age-adjusted rates of cardiovascular-related deaths can be up to five times higher than in high-income countries [25]. By 2030, CVD will be responsible for 75% of deaths worldwide, more than 24 million deaths, and will account for more deaths in LMICs than infectious diseases, maternal and perinatal conditions, and nutritional disorders combined [24–26]. Targeting preventable causes of CVD in LMICs, such as HAP, is imperative. To date, no field intervention trial has sufficiently demonstrated that reducing HAP can decrease CVD morbidity, leaving policy-makers reluctant to implement cleaner stove programs as a strategy to address CVD risk.

### Cardiovascular disease related to biomass fuel smoke exposure

There is a growing understanding that pulmonary inflammation caused by HAP affects cardiovascular health [27]. However, less is known about the mechanism by which HAP leads to CVD or the true burden of biomass fuel smoke exposure on CVD risk [1, 27]. Cross-sectional and longitudinal studies have found strong associations between ambient air pollution, measured by particulate matter (PM) levels, and an increased risk of cardiovascular-related death [27–32]. Chronic exposure to biomass fuels has been associated with a thicker carotid artery intima-media complex, higher prevalence of atherosclerotic plaques, and higher blood pressure [33]. PM less than 2.5 μm in diameter (PM_2.5_), including ultrafine particles, are small enough to deposit in alveoli, initiate inflammatory cascades, and enter the pulmonary circulation [34]. The Women’s Health Initiative Observational Study followed more than 65,000 women from urban areas for 6 years and found that an increase of 10 μg/m^3^ in ambient PM_2.5_ was associated with a 24% increased risk of cardiovascular events and a 76% increased risk of cardiovascular-related deaths [20]. However, little is known about the response curve of HAP on cardiovascular outcomes [35]. Investigators in Guatemala found that when biomass fuel smoke-related PM exposure was reduced by 50% via an improved biomass-burning stove, a reduction in blood pressure within a few months was found in a sample of women [36]. PM is believed to affect the circulatory system through increased blood pressure, inflammation, propagation of coagulation, and increased blood viscosity [27, 37–39]. Particularly, endothelial dysfunction and progression of atherosclerosis are believed to be an integral link between PM exposure and worse cardiovascular health [30]. There is clear evidence that ambient air pollution causes both acute [30–32, 34] and chronic endothelial dysfunction [40, 41], but the relationship with HAP has not been fully explored in intervention trials.

### Respiratory disease related to biomass fuel smoke exposure

The adverse health effects of HAP on respiratory health, and specifically its contribution to COPD, have been well documented [42–47]. A previous study in rural Peru found that 55% of COPD prevalence can be attributed to daily exposure to biomass fuel smoke [48]. Among women, biomass fuel smoke exposure was associated with a doubling in the odds of COPD [48] and chronic bronchitis [49], similar to that described in other studies [46]. Interventions in rural Mexico revealed a consistent relationship, with improved wood stoves being associated with reductions in respiratory symptoms [13, 50]. However, there is still an important gap in our understanding of how biomass fuel smoke exposure affects lung function decline [47]. Previous findings suggest a log-linear relationship between HAP and lower respiratory infections, i.e., a steep slope for PM_2.5_ levels below 100 μg/m^3^ and a less pronounced slope thereafter [35, 51]. This implies that very low levels of exposure need to be achieved to observe health benefits.

### Previous research on improved stoves

Improved cookstoves were introduced as a cost-effective strategy to reduce HAP [16, 44, 52–55] through more efficient combustion of biomass fuels and ventilation. Most modifications include closed combustion chambers and chimneys [47, 56]. Although improved cookstoves have achieved important reductions in HAP, both personal exposure and kitchen concentrations of environmental pollutants remain several-fold higher than World Health Organization (WHO)-recommended levels [57], and the effect of these achieved reductions on health outcomes has not always been evident [52]. For example, a randomized field trial of improved biomass fuel stoves in Guatemala did not lower physician-diagnosed pneumonia (primary outcome) in the intention-to-treat analysis (RR = 0.84, 95% CI 0.63–1.13) between children in the intervention and control arms [16]. Similarly, a recent, large-scale cluster-randomized trial in Malawi did not reduce childhood pneumonia with an improved biomass-burning stove intervention [58]. The lack of health effects for both of these trials is likely attributed to the continued use of polluting stoves and an inability of the intervention to achieve reductions in personal exposure below the WHO intermediate targets (35 μg/m^3^) of household air quality. Prior exposure-response analyses have found that the greatest risk reductions occur with much lower exposure levels that are unlikely to be achieved with improved biomass-burning stoves [2, 16, 35]. For example, in RESPIRE, the exposure-response analyses found that an expected reduction of 50% in personal carbon monoxide (CO) concentrations was associated with a lower incidence of physician-diagnosed pneumonia (RR = 0.82, 95% CI 0.70–0.98) but the intention to treat analysis did not show significant results. The authors attribute the difference in results between the intention-to-treat and exposure-response analyses to less exposure misclassification in the latter, i.e., the intention-to-treat analysis does not account for subject-specific exposures to HAP. Moreover, larger expected reductions may lower the risk of physician-diagnosed pneumonia even further. Thus, recent intervention efforts are shifting towards stoves that use cleaner fuels [53, 54, 59–62].

Current research has demonstrated that liquefied petroleum gas (LPG) fuels can significantly reduce HAP when compared to biomass fuels. However, there have been few studies that have reported on the relationship between direct measures of HAP and health outcomes using LPG stoves as an intervention to replace biomass stoves [54]. Studies in Guatemala and Bangladesh demonstrated PM reductions with LPG stove use that ranged from 45 to 90%, although these studies were cross-sectional and enrolled a small number of participants [53, 54, 61].

Additionally, few studies have linked LPG stove use to health outcomes [8, 59, 62–66], and even fewer have incorporated longitudinal follow-up of HAP and health [59]. Using retrospective, longitudinal data, a study in China concluded that women cooking with cleaner fuels, including LPG, were more likely to report better health and had a lower probability of chronic and acute diseases when compared to women cooking with biomass fuels [59]. A cross-sectional study in a rural village near Mexico City found that women cooking with biomass fuels had more respiratory symptoms and higher kitchen PM_10_ concentrations, compared to those cooking with LPG [67]. A cross-sectional study of 760 women in rural India found that 43% of those using biomass fuels had abnormal peak expiratory flow (PEF) readings when compared to 23% of those using LPG [62]. Cataracts have also been associated with the use of biomass fuels for cooking [2], and this also appears to be reduced with LPG. A case-control study along the Nepal-India border found that women using traditional cookstoves were 90% more likely to develop cataracts than women using a combination of biogas, LPG, and kerosene (OR = 1.90, 95% CI 1.00–3.61) [63]. This study, however, did not consider the effects of LPG stove use alone, and included kerosene [63], which has been classified by the WHO as a dangerous fuel source [57]. Overall, there is a lack of longitudinal research studies examining the health effects of switching from biomass fuel to LPG for cooking.

A major barrier to assessing the effect of LPG fuel use on HAP and health is stove stacking, in which families continue using their traditional biomass stoves after receiving an LPG stove. Since just 1 h per week of traditional stove use raises PM_2.5_ concentrations above WHO guidelines, even a small amount of stove stacking can negate many of the benefits of clean cooking technologies [68]. Previous research has shown that people who use LPG stoves like the speed of cooking, the cleanliness, and ease of use, but that the cost of fuel is frequently a barrier to adoption [69]. Additional barriers to exclusive adoption of LPG stoves include fears that LPG stoves are unsafe, lack of knowledge about their proper operation, a desire for more burners, and changes in the taste of food cooked on LPG stoves [69]. However, previous research on the adoption of LPG stoves has focused on situations where LPG must be purchased. To date, there is no research on factors that might hinder or facilitate adoption once cost is removed as an obstacle [69]. Thus, it is necessary to gain an in-depth understanding of factors that motivate families to adopt clean fuels and facilitate the exclusive use necessary to achieve the potential health benefits.

Previous research has rarely examined other consequences of stove interventions such as changes in diet and quality of life. Anderman et al. observed that households provided with methane biogas stoves had more diverse diets (measured by number of food groups) than households using a firewood stove [60]. Nonetheless, little is known about how LPG stoves might affect dietary patterns. One of the few studies that has looked at quality of life and biomass burning found that respiratory quality of life improved after installation of ventilated cookstoves in rural Bolivia [70]. To date, no intervention has assessed how a gas stove intervention affects quality-of-life outcomes.

There is a lack of studies with sufficient sample size and longitudinal follow-up to determine the health effects of LPG fuel use when compared to biomass fuel use. Additionally, few studies have collected high-quality environmental measurements of both kitchen and personal air quality. Furthermore, many studies have struggled to reduce HAP concentrations due to stove stacking. This study aims to address these gaps by conducting a longitudinal assessment of clinical outcomes, and personal exposure and kitchen HAP concentrations over 2 years, while explicitly investigating and incorporating behavior change into study activities. Understanding the factors influencing LPG adoption will enable us to better motivate exclusive LPG adoption and better quantify the potential impact of LPG stoves on exposure to HAP and health. Because no field intervention trial of LPG fuel use has convincingly demonstrated that a reduction of HAP decreases morbidity or mortality, policy-makers have been reluctant to invest in its more widespread adoption. This trial could provide evidence needed to justify investment in LPG as an effective public health intervention.

## Methods

### Study objectives

This study is a randomized, field intervention trial testing the efficacy of LPG stove use and fuel distribution, compared to traditional, open-fire stove use, as a strategy to reduce HAP and improve cardiopulmonary outcomes in the rural, high-altitude setting of Puno, Peru. LPG stove use will be monitored and compared to standard cooking practices to determine the relative effect of LPG adoption on HAP concentrations and subsequent improvements in cardiopulmonary outcomes over a 1-year period. As a secondary objective, in the second year of follow-up, we will measure intervention effectiveness by characterizing the sustainability of LPG among participants in the intervention arm and initial adoption of LPG among those in the control arm (Fig. 1).

**Fig. 1 Fig1:**
[figure not shown]
Expected study enrollment and timeline diagram

### Study setting and population

The trial will take place in rural areas surrounding the city of Puno in southeastern Peru (Fig. 2), on the shore of Lake Titicaca at 3825 m above sea level. Puno is the capital and largest city of the Puno Province which, in 2007, had a population of 230,000 inhabitants [71]. Study participants live in rural communities in the province of Puno, where biomass-burning, open-fire stoves are used for cooking [72]. Median distance to nearest house between all households in the study area is 101 m with an interquartile range of 56 to 189 m (Fig. 3). Median nearest distance to the highway for households in the study area is 1701 m with an interquartile range of 893 to 3103 m. Only 4% of households are within 100 m from the road.

**Fig. 2 Fig2:**
[figure not shown]
Location of all households in the study population and liquefied petroleum gas fuel purchase sites

**Fig. 3 Fig3:**
[figure not shown]
Barplot of nearest-neighbor distances between households in study area. Median distance to nearest house between households in the study area is 101 m with an interquartile range of 56 to 189 m

We seek to enroll 180 women, 90 in both the intervention and control arms. One woman per household will be enrolled. To be eligible for the trial, women must be aged 25–64 years, be the primary cook, be a full-time resident in their current location for at least 6 months, be capable of understanding study procedures, providing informed consent, and respond to questionnaires, use biomass fuels daily for cooking, and have a cooking area separate from their sleeping area. The latter criterion was added to exclude households that use biomass fuel stoves to heat their living space. Women will be excluded from participating if they plan to move from the area within 1 year, have hypertension (taking antihypertension medications, or systolic blood pressure ≥ 140 mmHg or diastolic pressure ≥ 90 mmHg) or a diagnosis of COPD (post-bronchodilator FEV_1_/FVC below the lower limit of normal of a reference population), smoke cigarettes daily, are pregnant or have plans to become pregnant in the next year, and have active pulmonary tuberculosis or are taking antituberculosis medications for pulmonary tuberculosis. Women in these communities speak Aymara (local language) and Spanish. Field staff members who will collect data from participants are native Spanish speakers, and at least one member of the field team who speaks Aymara will attend each visit.

### Intervention

Participants will be provided with an LPG stove, with three burners, that connects to an external gas tank (Fig. 4). Formative research showed that three-burner stoves were preferred by the community over the commonly available two-burner stoves. Stoves will be purchased from a local manufacturer (Industrias SURGES, Juliaca, Peru). Current open-fire stoves will not be replaced or destroyed by study personnel. LPG fuel will be locally purchased and delivered to intervention participants’ homes for the first year of the study. Control participants will receive vouchers to pick free fuel from distributors for the second year of the study. Before receiving an LPG stove, all intervention participants will attend a community meeting where they will observe a cooking demonstration and receive behavioral messages based on formative research to promote exclusive LPG stove use. As part of the cooking demonstration, participants will receive safety information and training on how to correctly operate and maintain the LPG stove. Correct and exclusive use of the LPG stove will be reinforced during the approximately bi-monthly gas delivery visits to the households.

**Fig. 4 Fig4:**
[figure not shown]
Three-burner liquefied petroleum gas stove that will be used for the intervention

### Study design

Each participant who is enrolled in the study will receive a set of baseline pre-intervention assessments and multiple follow-up assessments over 24 months. The 90 participants assigned to the intervention arm will receive a free LPG stove and free fuel delivery to their homes approximately twice monthly during the first year to ensure a steady supply (Fig. 5). Rate of gas use will be tracked by a field staff member. Participants will be assigned to the intervention or control arms with a 1:1 ratio using random permuted block sizes of 2, 4, and 6 [73]. The randomization schedule was created in R [74] by an investigator who will not be involved in the recruitment or baseline interviews of participants. Study-arm allocation will be masked from field staff in envelopes until baseline measurements are complete. A field staff member will then open the envelopes.

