**Fig. 5 Fig5:**
[figure not shown]
Delivery system through motorcycle for liquefied petroleum gas tanks

The study will be conducted over 3 years, with staggered enrollment over the first year. Our field team will start recruitment by meeting with the leaders of each community to explain the study, obtain approval to approach community residents for participation, and schedule community meetings before enrollment. Our team will use previously collected census data to identify potentially eligible households. At the beginning of the study, we will randomly determine the order in which communities and subsectors within communities will be visited. Each month for the first year, we will randomly select households within subsectors from the census list to obtain informed consent and assess eligibility. We aim to enroll 15 households each month.

A nurse will be present during enrollment and clinical evaluations to thoroughly explain the trial, the procedures, and answer questions. We will obtain verbal informed consent (i.e., waiver of documentation of consent) and we will leave a written copy of the Consent Form signed by study staff with each participant. Any serious adverse events will be identified by the study team who will generate electronic reports within 24 h after the event. Participants would be directed towards the nearest emergency health facility for appropriate medical care. However, since this is a low-risk study, we do not expect any serious adverse events.

After obtaining informed consent, all participants will be asked to answer questions about their sociodemographics, medical history and current clinical symptoms. Personal exposure and kitchen 48-h PM_2.5_ and CO concentrations will be measured for each participant at baseline and longitudinally during the first year. We will monitor nitrogen dioxide (NO_2_) in a subset of 100 participants (50 in both the intervention and control arms). Stove use will be assessed by continuously monitoring the temperature of LPG and traditional stoves. Health outcomes will be measured at baseline and repeatedly at different intervals in the first year (Fig. 6). Primary outcomes include respiratory symptoms, spirometry, blood pressure, endothelial function and carotid intima-media thickness, and quality of life. Secondary outcomes include dietary salt intake and other macronutrients, inflammatory markers of HAP in urine and blood, and exhaled CO.

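### Field staff open permuted-block envelopes while still recruiting, so up to about 70% of allocations could be guessed if women are handled one by one, and nearer 50–58% at consent

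*Protocol article*

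**What the plan says.** All of the following is in the protocol article, under Study design unless stated.

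- Allocation uses a "1:1 ratio using random permuted block sizes of 2, 4, and 6". No stratification factor is mentioned.
- The schedule was made "by an investigator who will not be involved in the recruitment or baseline interviews of participants".
- On concealment: "Study-arm allocation will be masked from field staff in envelopes until baseline measurements are complete". Then: "A field staff member will then open the envelopes".
- On recruitment: "Our field team will start recruitment by meeting with the leaders of each community". Candidates are not picked by the recruiter, because "we will randomly select households within subsectors from the census list to obtain informed consent and assess eligibility". The pace is given as "We aim to enroll 15 households each month".
- On the length of baseline: "Personal exposure and kitchen 48-h PM_2.5_ and CO concentrations will be measured for each participant at baseline".
- Under Intervention, the intervention arm receives a stove and home gas deliveries, so an opened allocation is visible.
- Under Study setting and population, field staff collect the data, and eligibility depends partly on measured blood pressure and spirometry.
- Blinding is described only for the readers of ultrasound images (Cardiovascular health outcomes) and for the urine and blood samples (Urine and blood markers).

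**The concern.** A sealed envelope protects the woman whose envelope it is. It does not stop staff from inferring the next allocation from those already opened. Permuted blocks return to balance every 2, 4 or 6 women, so guessing the arm that is currently behind beats chance, and the guesser need not know the block size. Keeping the schedule maker out of recruitment does not affect this, because the information comes from the opened envelopes.

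The people who could hold this running count belong to the field team that seeks consent, checks eligibility and takes the baseline readings. Foreknowledge could affect how hard a woman is encouraged to join, how a borderline reading is handled, or how baseline tests are conducted. Respiratory symptoms, spirometry and blood pressure are primary outcomes for which no assessor blinding is described, so the trial leans heavily on an unpredictable allocation.

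**Working it through.** **The plan's own figure.** The article gives no figure for predictability. Its only calculation, the sample size of 85 or 63 per arm, reproduces but has no bearing here.

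**Inputs.** Block sizes 2, 4 and 6 at 1:1, total 180, about 15 women a month, and a baseline of at least 48 hours come from the article. Three assumptions are added, none of them stated there: the block sizes are equally frequent, there is one unstratified sequence, and accrual is even.

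**Step 1: the ceiling, with every earlier envelope already open.** In a block of 2m women, guessing the arm with fewer allocations so far gives an expected number of correct guesses of m + 2^(2m−1)/C(2m, m) − 1/2.

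| Block size | Expected correct | Share |
|---|---|---|
| 2 | 1 + 2/2 − 0.5 = 1.500 | 75.0% |
| 4 | 2 + 8/6 − 0.5 = 2.833 | 70.8% |
| 6 | 3 + 32/20 − 0.5 = 4.100 | 68.3% |

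With equally frequent sizes: (1.500 + 2.833 + 4.100)/(2 + 4 + 6) = 8.433/12 = 70.3%. Simulating 180 allocations with block boundaries unknown gives 70.2% for this rule, and 70.3% for an optimal guesser who knows the set of sizes. Chance is 50%. Only about 4% of allocations can be known with certainty when boundaries are unknown.

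**Step 2: how many earlier envelopes are still sealed at consent.** Fifteen women in about 30 days is one every 2 days. Baseline takes at least 2 days. So about 2/2 = 1 woman or more is still in baseline, with her envelope closed, when the next one is approached.

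**Step 3: guessing with sealed envelopes outstanding** (same simulation).

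| Earlier envelopes still sealed | Correct guesses |
|---|---|
| 0 | 70% |
| 1 | 58% |
| 2 | 55% |
| 3 | 52% |
| 5 | 50% |

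At consent the realistic range is therefore about 50–58%. It rises towards 70% late in a woman's baseline, as the envelopes before hers are opened.

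**Step 4: does block size 2 matter?** Without it, the ceiling is (2.833 + 4.100)/(4 + 6) = 69.3%, one point lower. With one envelope outstanding, blocks of 4 and 6 give 59%, slightly worse than the 58% for 2, 4 and 6.

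**Step 5: opening by monthly group.** If all 15 women finish baseline before any of their envelopes is opened, the first woman faces none outstanding, the second one, the third two, and so on. The rates by position are about 70%, 58%, 55%, 52% and 51%, then 50% for the other ten. The average is (0.70 + 0.58 + 0.55 + 0.52 + 0.51 + 10 × 0.50)/15 = 7.86/15, or about 52%. A direct simulation of groups of 15 also gives 52%.

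**The case against.** The strongest case against the point is that the article contains no error here. It does not say that envelopes are opened singly or in sequence, and its wording is compatible with opening a month's envelopes together. Such detail is commonly left to the full protocol or a field manual. That stands, and it is why the figures are conditional.

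A reader might infer that staff can guess about 70% of allocations before consent and baseline. The documents do not support this. Each envelope stays closed through a baseline of at least 48 hours, so at the stated pace one or more earlier allocations are normally unknown when the next woman is approached. Seventy per cent is the ceiling for strictly serial processing, or for the moment just before an envelope is opened, when nothing remains to influence.

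A reader might also blame the blocks of two, or suppose that staff have been told the block sizes. The first is not borne out by the arithmetic, and nothing in the article says the second.

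The safeguards are real. Households are drawn at random from a census, block sizes vary, the schedule maker is independent, blood pressure is read by an automatic monitor, spirometry has central quality control, and the SGRQ is described as self-completed. They narrow the scope for bias. They leave open the encouragement to consent, the handling of borderline eligibility readings and the conduct of effort-dependent tests.

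**Conclusion.** The point holds as a modest, conditional weakness in allocation concealment. In an open trial, a member of the field staff opens envelopes from a small-block sequence while the field team is still enrolling and measuring. If envelopes are opened as each baseline ends, which is the natural reading but is not stated, correct guessing could reach about 70% under serial processing and is more likely about 50–58% at consent.

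The size rests on the three assumptions listed in the working. Longer baselines or bunched recruitment would lower the rate at consent. These are guessing rates: the documents give no basis for turning them into a bias in any outcome, and they do not show that the trial's results would be invalid. If the full protocol already opens envelopes by group, the point falls away. It is worth raising because the remedy is cheap.

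**What to change.** State in the allocation procedure that each woman is given her sequence number at enrolment, and that no envelope is opened until every woman in that month's recruitment group of about 15 has completed consent, eligibility and baseline. Open the group's envelopes directly before the intervention group meeting. This fits the monthly selection of households and the community meeting that already precedes stove delivery. Only the first woman in each group then stays clearly predictable, with a small residue for the next two or three.

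The cost is one procedural sentence and a wait of up to a few weeks between baseline and allocation for women measured early in the month. The existing schedule can be kept, including blocks of two. The Trial status section says enrolment had not begun when the article was submitted. If recruitment is now under way, the rule can still be applied to the remaining groups.
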